### **3.1.4 Study design, methodology, study plan**

Persons aged 65 years and older will be recruited in the two selected districts of Nakhon Phanom Province and followed weekly for one year to identify any new episodes of ARI or SARI. Baseline information will be collected from all participants, including functional status and frailty indicators, chronic diseases, smoking history, and variables related to socioeconomic status. Participants will be asked how far the closest health center is from them and household latitude and longitude will be collected in order to calculate distances to medical facilities. ARI will be defined as a new onset of cough or worsening of chronic cough, with or without fever.

SARI will be defined as new onset of cough, worsening of chronic cough or difficulty breathing with a fever  $\geq 38^{\circ}$  Celsius that requires hospitalization. Nasal and nasopharyngeal samples taken from persons with ARI or SARI will be tested using real-time reverse-transcription polymerase chain reaction (rRT-PCR) for influenza and respiratory syncytial viruses. The incidence of laboratory-confirmed, influenza-associated ARI and SARI will be compared between vaccinated and unvaccinated cohort participants, controlling for baseline functional status and underlying medical conditions that might confound the primary association. Data on costs of visits for ARI and SARI for pneumonia or acute respiratory illness will be collected, along with information on the costs of the vaccination campaign, to determine the cost per influenza episode averted and the value for money of the immunization campaign. Results will assist the Thai Ministry of Public Health to make informed decisions related to improving vaccination coverage among the elderly in Thailand.

In addition to vaccine effectiveness and cost effectiveness data, this study will also take the opportunity to measure the effect of ARI and SARI on functional status among the elderly, measure the incidence of influenza-associated COPD exacerbations among those with ARI or SARI, evaluate humoral immune response of IIV3 through measurement of hemagglutination inhibition assay (HAI), and measure the incidence of respiratory syncytial virus (RSV) among the elderly with ARI or SARI.

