Vaccination: Cohort participants, along with all persons aged 65 years and older in the districts identified by the MOPH for increased IIV3 coverage, will be eligible for influenza vaccination through routine vaccine delivery strategies used by the MOPH. No vaccine will be provided as part of this protocol. The study will be enrolling participants from two districts in Nakhon Phanom, That Phanom and Plapak. According to the Nakhon Phanom Provincial Health Office, the vaccination rate in 2014 was calculated to be 52% and 28% in That Phanom and Plapak, respectively. This VE study will follow a pilot program of the MOPH to increase vaccination among the elderly through a concentrated and focused vaccine campaign in the elderly. This year, due to planned vaccination campaigns, we expect the vaccination rate to be around 50% in both districts. A companion study to this protocol, already underway, will evaluate the coverage achieved by the pilot campaign as well as measure factors associated with receipt of the vaccine in this age group.

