Cost data: Records from the Provincial Medical Office and the National Health Services Office will be used to determine the cost of the vaccination campaign, which will be converted into a per capita cost per vaccinee. Data from the Provincial Medical Office will also be collected on average cost of outpatient visits for acute respiratory infection and inpatient admissions for pneumonia. We will also account for indirect costs of missing work days for elderly and their caregivers, and transportation cost. This information will be used to determine the cost-effectiveness of IIV3 among the elderly.

Functional Status:

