## **5. Objectives**

### **1. Primary Objectives**

1.1: Measure the incidence of laboratory-confirmed influenza-associated ARI and SARI among a cohort of persons aged 65 years and older in 2 districts in Nakhon Phanom Province and calculate vaccine effectiveness by comparing incidence between persons who did and did not receive IIV3, controlling for potential confounders.

1.2: Assess the medical costs (direct and indirect) associated with influenza infections among the elderly and estimate the savings from vaccination based on varying levels of vaccine coverage, and evaluate the value for money of the influenza vaccine campaign program for persons aged 65 years and older

1.3: Among persons aged 65 years and older with COPD, measure the incidence of influenza-associated COPD exacerbations meeting ARI or SARI case definitions, and all-cause exacerbations and compare incidences between vaccinated and unvaccinated persons

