#### **7.1.5 Number of participants**

Sample size for cohort: The cohort sample size is calculated assuming a 50% vaccination rate, 80% power, a probability of committing a type I error of 5% and an incidence of influenza-associated ARI of 6% per year. With an expected VE of 40% based on our population's age and past studies (12, 16, 17), the required sample size is 2,724. Given a 15% loss to follow-up, a total of 3,133 persons should be enrolled, and assuming a 10% refusal rate, a total of 3,446, or, for simplicity, 3,500 individuals need to be selected

These sample sizes were calculated in OpenEpi.com(47) using the Fleiss Method with a correction factor as follows:

Fleiss Method:

$$n_1 = \frac{[Z_{\alpha}\sqrt{(r+1)\bar{p}\bar{q}} + Z_{1-\beta}\sqrt{rp_1q_1 + p_2q_2}]^2}{r(p_1 - q_1)^2}$$

$$n_2 = rn_1$$

where  $n_1$  is the number of cases and  $n_2$  is the number of controls,  $\bar{p}$  is the average exposure in the population,  $\bar{q}$  is  $1-\bar{p}$ ,  $p_1$  is the proportion of cases with the exposure,  $q_1$  is  $1-p_1$ ,  $p_2$  is the proportion of controls with exposure and  $q_2$  is  $1-p_2$ .

To account for the use of a normal distribution to approximate a binary function, a continuity correction is applied to  $n_1$  as follows to calculate the final sample size,  $n_{cc}$ :

$$n_{1cc} = \frac{n_1}{4} \left[ 1 + \sqrt{1 + \frac{2(r+1)}{n_1 r |p_2 - p_1|}} \right]^2$$

$$n_{2cc} = rn_{1cc}$$

where  $n_{1cc}$  and  $n_{2cc}$  are the corrected sample sizes of  $n_1$  and  $n_2$ , respectively.

Sample size for changes in functional status related to ARI or SARI: We will select matched pairs and compare functional status (measured on a 10 point scale by the VES-13) three-four weeks after the onset of an influenza-associated ARI or SARI to a control who has not had an ARI or SARI. As functional status is measured on continuous scale of 1-10, a matched dependent  $t$  test is used to compute sample sizes. We have used the PROC POWER procedure in SAS

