### **For primary objective 1.2 (Direct and Indirect costs)**

When a participant becomes ill due to an ARI or SARI, we will train health volunteers to ask them about their costs associated with the infection with an electronic questionnaire CRF 1 week after recovering from their illness. If the participant went to a public health center or hospital, staff authorized by the hospital director will check their medical records to determine the cost of the visit. If the participant went to a private clinic, the standardized questionnaire will ask about the amount of money they and their insurance spent in order to treat/get treated for their illness including all laboratory and examination tests, clinician fees, hospital fees, medication fees. The questionnaire will also ask all participants regarding cost of over-the-

counter medications including herbal or traditional medicine costs, transportation fees, and questions to determine how much income their household lost due to missed work days of the elderly participant and of caregivers who take care of the participant to calculate indirect cost.

Records from the Provincial Medical Office and the National Health Services Office will be used to determine the cost of the vaccination campaign, which will be converted into a per capita cost per vaccinee. Data from the Provincial Medical Office will also be collected on average cost of outpatient visits for acute respiratory infection and inpatient admissions for pneumonia.

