## **7.9 Data Analysis**

In order to evaluate the primary research question – the vaccine effectiveness of the inactivated trivalent IIV3 vaccine in the elderly - we will use Poisson regression with person-time at risk as an offset. The outcome variable will be the number of influenza associated ARI or SARI events in each given year of life among 2 groups, elderly who have been vaccinated with IIV3 and elderly who have not. The resulting count data will account for multiple outcomes in the same participant. We will also employ GEE methodology to the Poisson regression to account for geographical clustering by cases and correlation between outcomes in individuals with repeated measures. We can control for other predictive variables that may be associated with

underlying disease such as age, co-morbidities and distance to health facility. To reduce any potential non-random loss-to-follow up bias, we will use propensity score matching in addition to controlling for confounders. To address the other primary study question regarding cost, we will obtain estimates of direct and indirect costs from each of the groups and apply differences to the adjusted risks to arrive at the adjusted cost differences between elderly who have been vaccinated and elderly who have not been vaccinated.

In order to measure the effect ARI and SARI have on functional status (secondary objective 2.1) we will compare change in functional status among those that did and did not experience ARIs or SARIs by matching participants to one control when they become sick to see if there is a significant difference in functional status measurements. We will use a nested case control study to compare the two groups. By matching those who experienced a first ARI or SARI with those who had not on age ( $\pm 5$  years), sex, influenza vaccination and most recent functional status measurement ( $\pm 1$  point), we can account for unknown confounders that may cause a change in functional status while controlling for known confounders.

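### An average campaign cost per vaccinee suits value for money at the observed coverage, but not the varying-coverage part of primary objective 1.2

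*Protocol*

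**What the plan says.** Section 7.5.1, under primary objective 1.2, says that Provincial Medical Office and National Health Services Office records will be used to determine "the cost of the vaccination campaign, which will be converted into a per capita cost per vaccinee". The cost paragraph of section 3.1.4 states the same conversion. The protocol describes no other treatment of campaign cost.

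Objective 1.2 in section 5 asks the study, among other things, to "estimate the savings from vaccination based on varying levels of vaccine coverage" and to "evaluate the value for money of the influenza vaccine campaign program for persons aged 65 years and older". Section 3.1.4 adds that the cost data serve "to determine the cost per influenza episode averted and the value for money of the immunization campaign".

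On the benefit side, section 7.9 will "apply differences to the adjusted risks to arrive at the adjusted cost differences between elderly who have been vaccinated and elderly who have not". That is one difference per person, with no term for coverage.

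On coverage, section 3.1.4 reports that "the vaccination rate in 2014 was calculated to be 52% and 28% in That Phanom and Plapak, respectively", and expects about 50% in both districts in the study year.

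**The concern.** A campaign may carry costs that do not depend on the number of doses given, such as planning, training and promotion. Dividing the total by the number vaccinated spreads those costs over the people reached at one particular coverage. The resulting average describes that campaign correctly. At lower coverage the same fixed cost falls on fewer people, so the average is too low.

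The protocol wants results at several coverage levels, but the only campaign cost input it defines is this average. Once the cost lines have been collapsed into one figure, the average cannot be recalculated for another coverage level without returning to the records. At stake is whether the coverage scenarios tell the ministry anything beyond the single observed point. The vaccine effectiveness estimate is not affected.

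**Working it through.** The protocol states no campaign cost, saving or break-even coverage, so there is no figure of its own to reproduce.

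**Inputs**
- N = 9,000 elderly in the two districts (section 7.5.2: about 6,000 and 3,000). The seroconversion sample size in section 7.1.5 uses about 15,000. The choice only rescales totals.
- Section 7.1.5 gives "an incidence of influenza-associated ARI of 6% per year", taken here as the rate in the unvaccinated, and an expected vaccine effectiveness of 40%.
- Coverage p: 28% (2014, Plapak) and 50% (expected), both from section 3.1.4.
- c = average campaign cost per vaccinee at 50% coverage, set to 1 unit. b = illness cost averted per vaccinee.
- f = share of campaign cost that is fixed at 50% coverage. This is **an assumption**, shown at 20%, 40% and 60%.

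**Step 1: the average carried to every coverage level**

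Net saving = N × p × b − N × p × c = N × p × (b − c).

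This is proportional to p and has the sign of (b − c) at every p above zero. With b = 1.1c it is 9,000 × 0.28 × 0.1 = +252 units at 28% and 9,000 × 0.50 × 0.1 = +450 at 50%. With b = 0.9c the results are −252 and −450.

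Episodes averted per vaccinee = 0.06 × 0.40 = 0.024. Gross campaign cost per episode averted = c / 0.024 = 41.7c at every coverage. If 6% is instead the overall rate at 50% coverage, the unvaccinated rate is 0.06 / (1 − 0.5 × 0.4) = 0.075. Episodes averted are then 0.030 per vaccinee and the cost is 33.3c, again the same at every coverage.

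**Step 2: campaign cost split into fixed and per-dose parts**

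F = f × c × N × 0.5 and v = (1 − f) × c, so cost per vaccinee at coverage p = c × [(1 − f) + f × 0.5 / p].

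At p = 28%:

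| f | True cost per vaccinee | Error of the average (1 / true − 1) | Cost per episode averted (true / 0.024) |
|---|---|---|---|
| 20% | 1.157c | −13.6% | 48.2c |
| 40% | 1.314c | −23.9% | 54.8c |
| 60% | 1.471c | −32.0% | 61.3c |

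**Step 3: when the verdict changes**

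At 28% coverage the average shows a saving if b > c. The split shows a saving only if b exceeds the true cost in the table. The two disagree only when b/c lies between 1 and 1.157, 1.314 or 1.471 for the three values of f. Below 1 both show a loss, and above the upper limit both show a saving.

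Example with f = 20% and b = 1.1c at 28%: benefit 9,000 × 0.28 × 1.1 = 2,772; fixed cost 0.2 × 9,000 × 0.5 = 900; per-dose cost 0.8 × 2,520 = 2,016; net 2,772 − 900 − 2,016 = −144, against +252 in step 1.

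Break-even coverage is F / [N × (b − v)] = 0.5f / (b/c − 1 + f). With b = 1.1c this is 33%, 40% and 43% for f = 20%, 40% and 60%.

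**The case against.** The strongest reply is that the protocol never writes out a coverage formula. Sections 3.1.4 and 7.5.1 describe how the cost is obtained, section 7.9 is brief, and the scenario model could be set out in an analysis plan. This stands. A reader might infer that the protocol commits itself to the same verdict at every coverage level, but the text does not go that far. That result follows only if the average is carried over unchanged.

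Second, the clause on savings at varying coverage can be read as illness costs averted, before campaign cost, with value for money judged only for the campaign as run. This also stands as a reading. The average is then adequate, and the point applies only to scenarios that net off campaign cost. Nor does the protocol promise a break-even coverage, so its absence is no fault.

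Third, a reader might infer from the 52% and 28% that one average cannot describe both districts. The documents do not support this. Those are 2014 rates, about 50% is expected in both districts in the study year, and nothing prevents a calculation by district. Nor could the two districts validate a split, since two totals fit two unknowns exactly.

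Fourth, one might infer that the average overstates cost at high coverage. That holds only if per-dose cost stays flat. People harder to reach may cost more to vaccinate, so the direction there is open.

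What the reply does not remove is that the average is the only campaign cost input named, and that collapsing the records into it discards what another coverage level needs.

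**Conclusion.** The point holds as a limited, practical one. The average cost per vaccinee is valid at the coverage observed and not suited to other coverage levels. If it is used there, with the per-person benefit of section 7.9, the amount of net saving varies with coverage, but its sign and the cost per episode averted cannot.

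The size rests on a fixed share that the protocol does not give. Over an assumed 20% to 60%, cost per vaccinee at 28% coverage is understated by 14% to 32%. The change of verdict in the example depends on a benefit chosen close to the average cost. If benefit per vaccinee is below the average cost, or above about 1.16 to 1.47 times it depending on the fixed share, the verdict at 28% stays the same.

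**What to change.** When the Provincial Medical Office and National Health Services Office records are extracted, classify each campaign cost line as fixed or per-dose as far as the records allow. Then:

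- Keep the average cost per vaccinee for value for money at the observed coverage.
- In any coverage scenario that nets off campaign cost, use total cost = F + v × p × N.
- Report a sensitivity range on the fixed share, and on per-dose cost at higher coverage.
- State whether savings at varying coverage are before or after campaign cost.

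The records are already to be obtained and no new participant data are needed. The cost is the classification work and a stated convention for allocating shared items. The protocol does not show how finely the records are itemised. If they do not allow a split, the fixed share has to be varied as an assumption.

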### **For secondary objective 2.1 (Functional status)**

Participants will be scored on their VES-13 results every six months. The Vulnerable Elders Survey (VES-13) is a function-based questionnaire that was developed to screen elderly 65 years of age or greater in the community to determine their risk for health deterioration (7, 8). The questionnaire asks elderly to self-report their age, health, limitations in physical function and functional disabilities, and takes an average of less than five minutes to complete(7, 8). This tool can be administered over the phone or in person. Each response to each question on the form has a point value attached ranging from 0 to 3 points, and it is scored by adding up points based on the responses received, up to 10.(8) Scores  $\geq 3$  indicate frailty associated with increased mortality.

In order to measure the impact of the first episode of ARI or SARI on functional status, we will conduct a nested case-control study of participants recovering from an ARI or SARI. Participants who experience their first ARI or SARI after enrollment will be matched with one cohort participant who has not yet experienced an ARI or SARI based on age ( $\pm 5$  years), sex, influenza vaccination and most recent functional status measurement. Interviews will be conducted three to four weeks after the onset of ARI or SARI in the case and both cases and controls will be compared with respect to changes in functional status measurement using a multinomial logistic regression to control for other potential confounders. Beginning from January 2016, when a complete dataset for vaccination and functional status will be available, these interviews will be conducted until the required sample size of 115 matched pairs of cases and controls are met.

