In order to measure the impact of the first episode of ARI or SARI on functional status, we will conduct a nested case-control study of participants recovering from an ARI or SARI. Participants who experience their first ARI or SARI after enrollment will be matched with cohort participants who have not yet experienced an ARI or SARI based on age ( $\pm 5$  years), sex, influenza vaccination and most recent functional status measurement. Interviews will be conducted three to four weeks after the onset of ARI or SARI in the case and both cases and controls will be compared with respect to changes in functional status measurement (VES-13 score  $\geq 3$ ).

Elderly with COPD: In the standardized baseline questionnaire assessing functional status and medical conditions, participants will be asked whether they have been diagnosed with COPD. If they do, at the end of two years, the number of outpatient visits and inpatient admissions for exacerbations of COPD will be determined (by directly observing their medical records). A COPD exacerbation is defined as “a sustained worsening of the patient's condition, from the stable state and beyond normal day-to-day variations that is acute in onset and may warrant additional treatment in a patient with underlying COPD” (11). We will use the collected nasal self-swabs or healthcare worker collected nasopharyngeal swab taken when the participant was experiencing an ARI or SARI to confirm whether the COPD exacerbations the participant experienced were influenza-associated. At the end of the study, the incidence of all-cause COPD exacerbations and laboratory confirmed influenza-associated COPD exacerbations among the elderly with COPD who fit the ARI or SARI case definitions will be calculated. The incidence among those who were vaccinated will be compared to those who were not vaccinated.

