## **7.4 Discontinuation Criteria**

Participants in the community study, who choose to withdraw from the study, move permanently outside of the selected sub-district during the study or die during the study period will be considered discontinued. The study will be terminated if any major event results in the inability to contact majority of study participants or to collect adequate data and keep the data safe.

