The nasal and nasopharyngeal swabs will be picked up from all health centers involved in the study on a weekly basis by hired study staff and transported to the NIH laboratory in Nonthaburi in a liquid nitrogen tank for testing. They will be tested by rRT-PCR for the presence of ribonuclease P (RNase P). RNase P is commonly used as an internal control in PCR to indicate the presence of human cells. rRT-PCR involves using the nasal swab samples placed inside VTM and mixing them with a buffer before being incubated at 70 degrees Celsius. Then the RNA is extracted from the mixture using Nucleospin RNA virus. The RNA is eventually mixed with a diluted solution of primers and probes and placed onto a PRC plate or in a PCR tube with a mixture of reagents. This PCR tube or plate is then placed inside a Realtime PCR machine at different temperatures and for various time periods. The results are converted to cycle thresholds (4). The cycle threshold number in rRT-PCR indicates how fast the target is detected and tends to correlate with the amount of the target detected. We will consider samples with

cycle thresholds  $<37$  for RNase P to be adequate (4). We will also record the cycle threshold for additional classifications. The results of the PCR testing (whether the participant has influenza or RSV) will be added to the centralized database in Nonthaburi.

As mentioned above, health volunteers will be trained to make weekly visits/calls to the homes of the participants and answer a short electronic questionnaire case report form (CRF) accompanying the visit/call about each participant's incidence of ARI which will be collected on a hand held computer and synced into a centralized data base at That Phanom and Plapak district hospitals at least once a week.. They will also be asked to assess the elderly participant's functional status and cost of having an ARI after any participant recovers from an ARI/SARI at the specific time period; information will be recorded onto a questionnaire CRF on a hand-held computer as well. CRFs will have each participant's unique identification number input and the health volunteer will transfer data regularly to the district hospitals and the centralized database.

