### Functional status sub-study

One hundred fifteen elderly with a first ARI or SARI will be interviewed within three to four weeks of the onset of their illness to determine their VES-13 score. A participant who has not had ARI or SARI since the start of the study will be randomly selected from among those who match the case on age ( $\pm 5$  years), sex, influenza vaccination and most recent functional status measurement and interviewed for functional status at the same time as the case.

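### The protocol contradicts itself on whether the functional-status interview is timed from onset or from recovery, and following the recovery rule may understate the effect of ARI/SARI on function

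*Protocol*

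**What the plan says.** **Onset rule.** Section 7.5.1, under secondary objective 2.1: "Interviews will be conducted three to four weeks after the onset of ARI or SARI in the case". Eligibility there needs only a first episode: "Participants who experience their first ARI or SARI after enrollment will be matched with one cohort participant". The participant-selection text in 7.5.2 agrees: "One hundred fifteen elderly with a first ARI or SARI will be interviewed within three to four weeks of the onset of their illness". So do section 7.5.3 and the paragraph of 7.5.1 on self-swab kits. That paragraph separates the two follow-up forms in one sentence: functional status three to four weeks after onset, costs one week after recovery.

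**Recovery rule.** A later paragraph of 7.5.1 has volunteers assess "functional status and cost of having an ARI after any participant recovers from an ARI/SARI at the specific time period". The paragraph on clinic and hospital visits likewise places both questionnaires after recovery. Form 4c asks whether the participant has recovered and how many days ago, then tells the caller to book both questionnaires for one week after the reported recovery.

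**Source of cases.** Sections 3.1.4 and 7.5.1 both describe a "nested case-control study of participants recovering from an ARI or SARI".

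**Accrual and losses.** From January 2016, "these interviews will be conducted until the required sample size of 115 matched pairs of cases and controls are met". Section 7.4 says that participants who "die during the study period will be considered discontinued", as are those who withdraw or move away. No text says what happens to a matched pair whose case or control cannot be interviewed.

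**The concern.** Objective 2.1 asks how far a first ARI or SARI changes functional status. If the interview waits for recovery, whether a case is measured depends on how the illness went. A case still unwell at four weeks, or too ill to answer, plausibly has one of the worst functional results and is the one form 4c would not schedule. Each case has one control, interviewed at the same time, so an uninterviewed case yields no pair. Because accrual runs to a fixed number of pairs, the final sample looks complete at 115 whatever was missed. Wording on who is interviewed and when belongs to the protocol. A statistical analysis plan could not recover interviews that were never scheduled.

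**Working it through.** **1. Do the two rules agree in practice?** The onset rule sets the interview at days 21 to 28 after onset. Form 4c sets it at recovery day + 7. Both hold only if recovery falls between day 21 − 7 = 14 and day 28 − 7 = 21.

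- Recovery before day 14: form 4c books the interview too early by the onset rule.
- Recovery after day 21: it books it too late.
- No recovery reported: form 4c books nothing.

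So the conflict matters for every case outside one week of recovery times. Early interviews of quick recoverers could push the estimate the other way, if function is still improving at that point.

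**2. The protocol's own figure.** Section 7.1.5 gives means of 4 and 5 (difference 1), SD 3, correlation 0.2, type I error 0.05 (taken as two-sided) and 80% power. With 3 as the SD in each group, the SD of the paired difference is 3 × √(2 × (1 − 0.2)) = 3.795. The exact paired t calculation then gives 115 pairs and power 0.800, so the figure reproduces. Read literally, with 3 as the SD of the difference, it would be 73 pairs. The power figures below use 3.795. No loss allowance is stated for the 115.

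**3. What missed cases could do.** Let *f* be the share of cases never interviewed and *e* their mean worsening relative to controls. If the true mean over all cases is 1, the interviewed cases show (1 − *f* × *e*)/(1 − *f*). Neither *f* nor *e* is in the documents; the values here are assumptions.

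| *f* | *e* = 1 | *e* = 3 | *e* = 5 |
|---|---|---|---|
| 2% | 1.00 | 0.94/0.98 = 0.96 | 0.90/0.98 = 0.92 |
| 5% | 1.00 | 0.85/0.95 = 0.89 | 0.75/0.95 = 0.79 |
| 10% | 1.00 | 0.70/0.90 = 0.78 | 0.50/0.90 = 0.56 |

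Power at 115 pairs, for *e* = 3 and *e* = 5, is 77% and 73% at 2% loss, 71% and 60% at 5%, and 59% and 34% at 10%. With *e* = 1, loss is unrelated to worsening, the bias is nil and power stays at 80%.

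**4. Pairs to start if 115 scored pairs are wanted.** 115/(1 − loss), rounded up: 118 at 2%, 122 at 5%, 128 at 10%, and 136 at the 15% used for the cohort.

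**The case against.** The onset rule is the better supported reading. It appears in the objective 2.1 text, in 7.5.2, in 7.5.3 and in the sentence that separates the two forms, and recovery is not a matching criterion. The recovery paragraphs bundle two questionnaires and add that each is done at its own time. This stands as evidence of intent, but form 4c, the scheduling instrument, says plainly otherwise.

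A reader might infer that a pair counts only once a recovering case has completed the interview, that lost cases are replaced by milder ones, and that the effect therefore is underestimated. The documents do not support this. No text sets such a counting rule, and the next eligible first episode may be of any severity. Controls aged 65 and over can also die, decline or withdraw, which could partly offset the loss. Nor is the quota the cause: analysing completers from a fixed set of pairs has the same bias. The quota only makes the loss less visible. The records needed to count missed cases largely exist (forms 4c, 4d and 4e), but the protocol does not require the count.

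The loss may also be small. ARI is any new or worsening cough. The cohort's 15% loss, if spread evenly, is 15% × 4/104 = 0.6% per four weeks over two years, or 15% × 4/52 = 1.2% over one. With an assumed worsening of 4 points, the observed difference would be 0.98 or 0.965. That is a fair lower benchmark. However, it averages over well and ill participants, and it leaves out cases who stay enrolled but have not recovered, whom form 4c would miss.

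Handling of deaths and missing scores may properly sit in an analysis plan that is not shown, so its absence here is not counted as a fault.

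**Conclusion.** The contradiction is established from the text: onset in some places, recovery in others, with cases labelled as recovering. The consequence is conditional. If the recovery instruction is followed, cases still ill are interviewed late or not at all, and the effect on function may be underestimated. The illustrative range runs from no bias, when loss is unrelated to worsening, to an observed difference of 0.56 against a true 1 at the extreme of the assumed grid (10% missed, mean worsening 5 points). The documents do not locate the study within that range, and early interviews of quick recoverers or losses among controls could work the other way. Even under the onset rule, deaths, withdrawals and cases too ill to answer leave no score, so reporting them is worthwhile either way. This concerns a secondary objective; it should be corrected, and it does not affect the vaccine-effectiveness analysis.

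**What to change.** - In sections 3.1.4 and 7.5.1 (including the clinic-visit and data-collection paragraphs) and on form 4c, delete the word recovering and the after-recovery condition for the functional-status questionnaire. Interview case and control three to four weeks after the case's onset, whether or not the case has recovered. The cost questionnaire stays at one week after recovery.
- In 7.5.1 and 7.5.2, take consecutive eligible first episodes, define the pair when case and control are matched, and report every matched pair without an interview with its reason (death, too ill, withdrawal), for cases and controls alike.
- Add a sensitivity analysis that puts death or being too ill to answer in the worst change category in both groups. Do not code these as VES-13 of 3 or more. Section 7.1.5 assumes a control mean of 4; with SD 3 and a normal approximation, about 63% (cut at 3) to 69% (cut at 2.5) would already be in that category. Since the analysis is of change, death would then register as no change for many participants.

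Cost: rewording, one form instruction and a reason code. There will be slightly fewer than 115 scored pairs, or a few more started (122 at 5% loss, 128 at 10%).
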